### Adverse events

All adverse events will be self-reported by the participants at 3, 6 and 9 weeks and assessed by the research staff for seriousness, expectedness and causality following the guidelines recommended by the National Health and Medical Research Council (NHMRC) position statement for monitoring and reporting of safety for clinical trials (https://www.nhmrc.gov.au/guidelines-publications/e112). In this study, an adverse event will be defined as any health-related unfavourable or unintended medical occurrence (sign, symptom, syndrome, illness) that develops or worsens during the period of the trial. Adverse events will be closely monitored until resolution or stabilisation is achieved or until it has been shown that the study intervention is not the cause of the injury. Participants will be asked to contact the research staff immediately in the event of a serious adverse event. Any adverse event sustained during the exercise programme will be recorded by the trainers and immediately reported to the research staff. The chief investigator will be informed of the adverse event and shall determine its seriousness and causality in conjunction with any medical staff treating the event. A serious adverse event that is deemed related to, or suspected to be related to, the exercise intervention will be reported to the ethics committee.

### Data management and archiving

All data will be de-identified, coded and stored on a Deakin University server that can be accessed only from password-protected computers. Any physical copies of the data recording sheet will be stored in locked filing cabinets at Deakin University (Burwood). All data will be checked monthly by the chief investigator to ensure that all protocols and ethical guidelines for data collection and analysis are followed. All study-related documents will be archived at Deakin University at the end of the study for a minimum of 6 years, which is in line with current ethical requirements.

### Dissemination plan

Findings derived from the primary outcome analysis of this trial will be reported in journal articles, which will include results regardless of the direction or magnitude of the effect. The results will also be presented at leading national and international conferences and clinical forums and to other relevant health professionals and stakeholders, as well as to the participants. All investigators will have the opportunity to be listed as an author of future publications, in accordance with the Australian Government National Health and Medical Research Council guidelines [60].

### Sample size calculation and statistical analysis

Gait speed, static balance and UPDRS-III at T6 will serve as primary outcome measures, with all other assessments and time points serving as secondary outcome measures. Based on the effect size observed in a recent study using a-tDCS during walking exercise [24], it is estimated that 42 participants randomised equally to three groups will be needed. Fourteen participants in each intervention group (a-tDCS, sham, control) will provide at least 80 % power to detect a 10–15 % difference in gait speed and static balance (centre of pressure), assuming a 5 % significance level. In functional assessments, a 10–15 % difference equates to an increase of 5.2 points on the UPDRS-III, which indicates a moderate clinically important difference [61].

A two-way, repeated-measures, mixed-design analysis of variance with factors time (T0 vs. T3 vs. T6 vs. T9) and treatment (a-tDCS vs. sham vs. control) will be used to determine any effect of the intervention on balance, gait speed and measures of brain physiology. False discovery rate analysis will be applied to determine when and where significance is found. An alpha level of *P* < 0.05 will be set to determine significance.

Where possible, we will obtain endpoint measures from all withdrawals and will include all randomised subjects in the final analysis. For participants who are lost to follow-up, missing data will be handled with multiple imputation. As this approach makes an untestable assumption that data are missing at random (i.e., missing data can be predicted from the observed data) [62], we will perform sensitivity analysis to evaluate the effect of potential non-random attrition [63]. Sensitivity analyses will employ simulation and will test a range of scenarios assuming plausible arm-specific differences in outcomes for individuals who were lost to follow-up [64].

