Transcranial direct current stimulation (tDCS) is a form of non-invasive brain stimulation that has been shown to modulate excitability of the M1 in a polarity-specific manner when applied for short periods (10–20 minutes). When anodal tDCS (a-tDCS) is applied to the M1, there is a transient increase (up to 90 minutes) in excitability and reduction SICI of underlying neurons [15], as well as widespread changes in activation of cortical and subcortical areas [16]. There is substantial evidence to suggest that the application of a-tDCS to the M1 results in improved motor function in healthy populations, including increased performance in skill and strength tasks [17, 18], and this may be especially true when tDCS is applied during concurrent motor practice or training [19].

The use of tDCS as an independent intervention in PD has produced promising results, with evidence for improved working memory and executive function [20, 21], reduced bradykinesia, and increased walking speed following tDCS [22]. Importantly, clinically significant improvements in the motor component of the Unified Parkinson’s Disease Rating Scale (UPDRS) have been reported following bilateral a-tDCS of the M1 [23]. A recent pilot study of eight participants reported for the first time that combined gait training and M1 a-tDCS showed promising improvements in walking and balance measurements, but the researchers in that study concluded that larger trials were required to produce definitive results [24].

Given the existing evidence for enhancements in neuroplasticity and motor performance following both PRT and tDCS as independent treatments, it is reasonable to conclude that the combination of these two interventions may further augment functional benefits in patients with PD. Indeed, a combination of a-tDCS and motor training appears to produce a compounding effect on motor performance and neurophysiological adaptations in healthy populations [25, 26] and stroke-affected individuals [27, 28]; however, the application of a-tDCS during PRT and balance training in PD is yet to be investigated.

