### Randomisation and blinding

Once recruited, simple randomisation using a computerised sequence generator will be used to allocate participants to one of three study groups (a-tDCS, sham or control). Opaque envelopes will be used to conceal the group allocation, which will not be revealed until after all data have been analysed. A researcher who is otherwise removed from the study will program the tDCS machine before PRT sessions to ensure double-blinding of both researcher and participant. Participants allocated to the control group will be notified of their allocation and will be asked to attend assessment sessions only.

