
A limitation of this study is the reduced sample size, which has been selected for the feasibility of conducting a one-to-one, 6-week exercise intervention. Despite this, sample size calculations indicate that any clinically significant benefits of combining a-tDCS with PRT will be detected statistically. If successful, pilot data from this study are vital to informing larger-scale clinical trials in patients with PD, and the additional investigation of underpinning neurophysiological mechanisms may also be translated to inform future treatment options for a range of other movement disorders.

The safe and inexpensive nature of a-tDCS is well suited for translation to existing and established PD rehabilitation programmes and services. While current pharmacological treatments in PD provide significant benefits to reduce the impact of some motor symptoms, bradykinesia and impaired postural stability often continue to impact patients significantly [3]. These symptoms have a detrimental effect of the quality of life of patients with PD and contribute to an increased risk of falls [4]. Rates of falls among patients with PD are twice as high as those in the general older population, with 46 % of people with PD experiencing recurrent falls each year [65, 66]. Falls often result in hospitalisation [67] as well as longer-term injuries such as fractures that further restrict physical capability and contribute to a cycle of secondary health complications and a loss of independence [68]. Effective interventions targeting balance and gait will reduce the burden of PD on the individual, family and carers, as well as the healthcare system. We anticipate that the findings of this study will inform large-scale randomised controlled trials aimed at implementing PRT and a-tDCS in community- and home-based settings to treat the motor symptoms of PD.

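### The Discussion says any clinically significant benefit of adding a-tDCS will be detected, which the stated power does not support

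*Protocol article*

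**What the plan says.** The protocol article, section 'Sample size calculation and statistical analysis', names three primary outcomes at T6: gait speed, static balance and UPDRS-III. On numbers it says "it is estimated that 42 participants randomised equally to three groups will be needed", and then that "Fourteen participants in each intervention group (a-tDCS, sham, control) will provide at least 80" per cent power for a 10–15 % difference in gait speed and centre of pressure at the 5 % level. The next sentence equates 10–15 % with 5.2 points on UPDRS-III and calls this a moderate clinically important difference, but attaches no power to it. The basis is given as "Based on the effect size observed in a recent study using a-tDCS during walking exercise". The Background describes the cited work: "A recent pilot study of eight participants reported for the first time that combined gait training and M1 a-tDCS showed promising improvements", and adds that its researchers wanted larger trials before drawing definite conclusions.

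The Discussion concedes that "A limitation of this study is the reduced sample size, which has been selected for the feasibility" of one-to-one training. It then says that the calculations nevertheless indicate that "any clinically significant benefits of combining a-tDCS with PRT will be detected statistically".

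**The concern.** The two sections make different claims. The sample size section claims a probability of at least 80 %, for two outcomes, at a stated range of differences. The Discussion claims detection without qualification, for any clinically significant benefit, and attributes this to the same calculation.

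This matters because the main hypothesis is what a-tDCS adds to progressive resistance training, so the key contrast is a-tDCS v sham, 14 against 14. If any worthwhile benefit would be detected, a non-significant result means that there is none. A trial of this size can support that reading only if the outcomes vary little between people, and the article does not say how much they vary. The study is meant to inform larger trials, so a false negative read in that way could discourage them.

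**Working it through.** **Inputs from the article.** 14 per group; power at least 80 %; significance level 5 %; target difference 10–15 % for gait speed and centre of pressure; 5.2 points for UPDRS-III.

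**Not given, so assumed.** Two-sided test; the comparison is a-tDCS v sham; SD as a percentage of the mean shown over 10–30 %; correlation r between baseline and T6 of 0 or 0.8, with 0.9 as a further case.

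**Reproducing the 80 %.** This cannot be done, because a percentage difference has no power until an SD is attached. The calculation is therefore inverted to find what SD the claim requires.

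**Step 1, detectable standardised difference d.** Normal approximation: d = (1.960 + 0.842) × √(2/14) = 1.06. Noncentral t with 26 degrees of freedom: d = 1.10. With 13 evaluable per group it is 1.15, and with 12 it is 1.20.

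**Step 2, largest SD that still gives 80 % power.** Unadjusted, SD = difference / d. With baseline adjustment, divide further by √(1 − r²), which is 0.6 at r = 0.8.

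- 10 % difference: 10 / 1.10 = 9.1 % of the mean; 9.1 / 0.6 = 15.2 %.
- 15 % difference: 15 / 1.10 = 13.6 %; 13.6 / 0.6 = 22.7 %.
- UPDRS-III, 5.2 points: 5.2 / 1.10 = 4.7 points; 4.7 / 0.6 = 7.9 points.

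At r = 0.9 the first two limits rise to 20.9 % and 31.3 %.

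**Step 3, does the choice of test change this?** Largest SD (% of the mean) for a 10 % and a 15 % difference:

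| Test | 10 % | 15 % |
|---|---|---|
| One-sided t | 10.4 | 15.5 |
| Three-group F test | 8.2–9.5 | 12.3–14.2 |
| Group-by-time interaction in the planned mixed ANOVA, correlation 0.8 | 11–16 | 17–23 |
| The same, correlation 0.9 | 16–22 | 23–33 |

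The ranges cover different assumed patterns of group means and, for the mixed ANOVA, of effects over time. The limits are of the same order as in Step 2 at comparable correlations.

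**Step 4, power with 14 per group over assumed SDs (noncentral t, two-sided 5 %).**

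| SD, % of mean | 10 % diff., unadjusted | 15 % diff., unadjusted | 10 % diff., r = 0.8 | 15 % diff., r = 0.8 |
|---|---|---|---|---|
| 10 | 72 % | 97 % | 99 % | >99 % |
| 15 | 40 % | 72 % | 81 % | 99 % |
| 20 | 25 % | 48 % | 56 % | 89 % |
| 25 | 17 % | 33 % | 40 % | 72 % |
| 30 | 13 % | 25 % | 29 % | 56 % |

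The SDs and r are assumptions. The table shows how far the answer depends on them; it does not estimate this trial's power.

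**Step 5, the detection sentence on the article's own figures.** If power is exactly 80 % at the target difference, the chance of missing it is 1 − 0.80 = 20 %. This step needs no SD.

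**Step 6, fewer than 14 evaluable.** At d = 1.10, power is 77 % with 13 per group and 73 % with 12.

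**The case against.** The strongest reply is that no arithmetic error has been shown. The effect size comes from a cited study that is not at hand, and a journal article commonly leaves the SD and correlation to the full protocol. Averaging gait over many steps and trials could give a high correlation between visits, and at r = 0.9 an SD of 21–31 % of the mean would still suffice. All of this stands. A reader might infer from the table that the 80 % is wrong, and the article does not support that inference.

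Four other strong readings also fail:

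- **The 10–15 % range contradicts itself.** It does not. The claim is of at least 80 %, which can hold at 10 % and be exceeded at 15 %. In that case the stricter SD limit, the one for 10 %, applies.
- **Needing 42 participants conflicts with choosing the number for feasibility.** A number limited by feasibility can still satisfy a calculation, and the Discussion presents it that way.
- **Power should be quoted at a third of the 5 % level because there are three primary outcomes.** The article plans a false discovery rate procedure, not that split.
- **The pilot's effect can be given a confidence interval from eight people.** Its effect is not reported here, and the 1.10 above is a detectable difference, not its result.

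On attrition, the one reported non-completer did not finish the intervention. That does not show that an outcome was lost, and the article plans to seek endpoint measures from withdrawals and to use multiple imputation. Imputation does not, however, restore all the lost information.

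The article also calls itself a pilot and names its size as a limitation, which softens the risk of misreading. None of this rescues the sentence about detection.

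**Conclusion.** The concern holds for the Discussion's sentence, at moderate severity. The calculation described supports at most a probability of 80 % or more, for gait speed and static balance, at the stated differences. It does not support certain detection, and it gives no power for UPDRS-III.

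The 80 % itself is uncheckable from the article. It corresponds to a standardised difference of about 1.10, assuming a two-sided 5 % comparison of 14 with 14. Unadjusted, that requires an SD of at most 9.1 % of the mean for a 10 % difference or 13.6 % for 15 %. With an assumed baseline correlation of 0.8 the limits are 15.2 % and 22.7 %, and a higher correlation would relax them further. For 5.2 points on UPDRS-III the limits are 4.7 points unadjusted and 7.9 points at r = 0.8. That the effect size came from an eight-participant pilot is a further reason not to state the power without its assumptions. The consequence is for interpretation: a non-significant a-tDCS v sham result would not exclude a worthwhile effect.

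**What to change.** Keep n = 42 and change the wording.

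1. In the sample size section, state that with 14 evaluable per group the a-tDCS v sham comparison has 80 % power, at two-sided 5 %, for a standardised difference of about 1.1 (about 1.2 with 12 per group).
2. For each primary outcome, including UPDRS-III, give the SD and baseline correlation that convert this into the outcome's own units, with their source.
3. Delete the Discussion's sentence on detection.
4. State in its place that results will be read from estimates with 95 % confidence intervals, and that a non-significant result does not exclude a worthwhile effect.

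Allocation, outcomes and analysis do not change. The cost is that the stated power will look less favourable.

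### The four-visit mixed ANOVA does not isolate the a-tDCS v sham comparison at T6 and makes T0 an outcome level, not a covariate; a baseline-adjusted T6 comparison would be safer and more precise

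*Protocol article*

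**What the plan says.** All the relevant text is in the Protocol article, section 'Sample size calculation and statistical analysis'.

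- Primary endpoint: "Gait speed, static balance and UPDRS-III at T6 will serve as primary outcome measures".
- Model: "A two-way, repeated-measures, mixed-design analysis of variance with factors time (T0 vs. T3 vs. T6 vs. T9"), crossed with "treatment (a-tDCS vs. sham vs. control) will be used to determine any effect of the intervention on balance, gait speed and measures of brain physiology". UPDRS-III, one of the three primary outcomes, is not in that list.
- Follow-up of the model: "False discovery rate analysis will be applied to determine when and where significance is found", with "An alpha level of *P* < 0.05 will be set to determine significance".
- Size: "42 participants randomised equally to three groups will be needed", that is 14 per arm.
- Missing data: "For participants who are lost to follow-up, missing data will be handled with multiple imputation". The same paragraph also plans to include everyone randomised and to run sensitivity analyses for non-random attrition.

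The Abstract and Discussion put the hypothesis as PRT with a-tDCS against PRT with sham. The article gives no visit correlations or standard deviations. It does not say whether the T6 result is a difference at T6 or a change from T0, or which error term that comparison uses.

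**The concern.** The trial asks one main question: does a-tDCS add to training at 6 weeks? The named model answers a broader one, whether three arms differ in profile over four visits. The T6 comparison of a-tDCS with sham has to be extracted afterwards, and the text does not fix how.

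This matters because the model's within-person error is pooled over all visits and all three arms. Pooling is valid for a contrast between two visits only if every pair of visits has the same difference variance (sphericity) and the arms have equal variance. The design gives reason to doubt both. T0 and T6 are 6 weeks apart with T3 between them, and two arms train while the control arm attends assessments only. If the pooled error is too small for a T0-to-T6 change, P values and intervals for the main comparison are too favourable.

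Separately, T0 predicts T6. Treating T0 as an outcome level forgoes the precision of covariate adjustment, and with 14 per arm that precision is worth having.

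**Working it through.** **The plan's own figure.** The only stated figure is at least 80 % power with 14 per arm, "assuming a 5 % significance level". For two arms the detectable standardised difference is (1.96 + 0.842) x sqrt(2/14) = 1.06 (1.10 with the t distribution). A 10 % difference then implies a coefficient of variation of 9.1-9.4 %, and a 15 % difference 13.6-14.2 %. No SD is given, so the power claim cannot be checked. It also does not say which contrast was powered.

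**Error strata.** With 3 arms x 14 people x 4 visits there are 3 x 13 = 39 df between subjects within arms, and 39 x 3 = 117 df for time x subject. Treatment is tested against the first; time and treatment x time against the second.

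**Reading A: change from T0 to T6 against the pooled time x subject error.** With unit variances, the pooled mean square has expectation 1 - r̄, where r̄ is the mean of the six visit correlations. The contrast needs 1 - r06, where r06 is the T0-T6 correlation. Hence

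estimated SE / true SE = sqrt[(1 - r̄) / (1 - r06)].

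- Compound symmetry 0.7: sqrt(0.30/0.30) = 1.
- AR(1) 0.7: r̄ = (3 x 0.7 + 2 x 0.49 + 0.343)/6 = 0.5705, so sqrt(0.4295/0.51) = 0.918.
- Baseline 0.5 with each later visit, 0.8 among later visits: r̄ = 0.65, so sqrt(0.35/0.50) = 0.837.

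Simulation under no effect (40,000-60,000 trials, complete data, two-sided 5 %, no adjustment for multiplicity):

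| Assumed structure | SE error, reading A | False positives, reading A |
|---|---|---|
| Compound symmetry 0.7 | none | 4.9-5.0 % |
| Slow decay (0.7/0.65/0.6 to 0.9/0.85/0.8) | 2.4-5.7 % too small | 5.7-6.6 % |
| AR(1) 0.5-0.95 | 7.2-8.7 % too small | 7.0-7.3 % |
| Baseline less correlated than later visits | 13.4-16.3 % too small | 8.7-10.3 % |
| Control arm with half the within-person variance | 8.5-16.3 % too small | 7.2-10.1 % |
| Control arm with 1.3 times the variance | 4.4 % too large to 4.5 % too small | 4.0-6.2 % |

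Repeat runs for AR(1) 0.5-0.9 lay within 6.8-7.6 %. Across the correlation patterns, the overall treatment x time F test rejects in 5.0-8.2 % uncorrected and 4.8-5.2 % with a Greenhouse-Geisser correction. The change contrast with its own two-arm error (26 df) rejects in 4.8-5.1 %.

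**Reading B: difference at T6 only, with the matching pooled cell error (MS between + 3 x MS within)/4.** This rejects in 4.8-5.1 % under every correlation pattern with equal variances. It moves to 4.1-6.5 % if visit SDs differ, and to 4.4-6.1 % if arm variances differ.

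**Precision of the T0-adjusted T6 comparison.** In large samples its SE relative to the change contrast is sqrt[(1 + r06)/2], and relative to the T6-only contrast sqrt(1 - r06²). For AR(1) 0.7, r06 = 0.49, giving 0.86 and 0.87. With 14 per arm, the simulated ratios of true SEs are slightly higher:

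| AR(1) | 0.5 | 0.6 | 0.7 | 0.8 | 0.9 |
|---|---|---|---|---|---|
| Adjusted / change | 0.81 | 0.83 | 0.89 | 0.93 | 0.97 |
| Adjusted / T6-only | 0.99 | 0.95 | 0.89 | 0.79 | 0.60 |

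The adjusted comparison rejects in 4.8-5.2 % over the correlation patterns run.

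**The case against.** The strongest reply is that the article does not commit the error. It does not say that follow-up comparisons use the pooled term, and it does not exclude a sphericity correction or contrast-specific errors. Such details are commonly left to an analysis plan, and with them the false-positive rate is about 5 %. This stands: the inflation is conditional on one reading.

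The primary outcomes are also defined at T6, with no mention of change, and the T6-only contrast holds its level under equal variances. This stands too, but that contrast leaves baseline unused.

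The stated false discovery rate step is not in the figures above. With Benjamini-Hochberg over an assumed family of nine change contrasts, the T6 a-tDCS v sham contrast was declared significant in only 1.7-3.2 % of runs with no effect anywhere, even with pooled error. Any rejection in that family occurred in 7-11 %. A smaller family, or real effects elsewhere in it, would raise the rate for the single contrast.

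Three stronger inferences are tempting and not supported:

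- That the ANOVA tests everything against one error term. It has two strata.
- That the T6 comparison carries a 7-10 % false-positive rate in general. Those values belong to reading A under the less favourable assumptions.
- That missed visits would shrink the arms. The protocol plans imputation and inclusion of everyone randomised.

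Finally, T0 as covariate or as time level can be called an efficiency choice. It is, but in a trial that names its sample size as a limitation the gain costs no data.

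**Conclusion.** The point holds in limited form. The named ANOVA does not identify the comparison that the trial is about, and it does not use baseline as a covariate. Under the change-from-T0 reading with pooled, uncorrected error, the unadjusted false-positive rate is about 5-10 %; it fell below 5 % only with a more variable control arm. Under the T6-only reading the level is about right with equal variances, but the true SE is larger than it need be. Adjusting for T0 reduces it by 1-40 % for AR(1) 0.5-0.9.

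A reader might infer that the plan as written inflates its error rate. The document does not support that, because it fixes neither the contrast, the error term nor the correction. All sizes rest on assumed correlations and variances, complete data and 14 per arm. The recommendation does not depend on which assumption is right: T0 adjustment held its level in every correlation pattern run and was more precise than either alternative.

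**What to change.** For gait speed, static balance and UPDRS-III, name as primary analysis the a-tDCS v sham difference at T6 adjusted for the T0 value, reported with its own error term and 95 % confidence interval. Either of two models will do:

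- ANCOVA at T6 with T0 as covariate.
- A mixed model for T3, T6 and T9 with treatment, visit, treatment x visit, T0 and T0 x visit, unstructured within-person covariance and Kenward-Roger degrees of freedom, with the ANCOVA as fallback if it does not converge.

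If the control arm may be less variable, fit the two compared arms alone or allow arm-specific residual variance; otherwise pooling across arms returns in the new model.

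Keep the stated multiple imputation, the attrition sensitivity analyses and the false discovery rate control. If the ANOVA stays for secondary outcomes, add a Greenhouse-Geisser or Huynh-Feldt correction and give each contrast its own error term.

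Cost: wording only, with no new data. Error degrees of freedom fall from 117 to about 25 (two arms: 28 - 3) or 38 (three arms: 42 - 4). The critical t rises from 1.98 to 2.06 or 2.02, which widens intervals by at most 2.06/1.98 - 1 = 4 % for a given SE. The Trial status section reports recruitment as ongoing, and group allocation stays concealed until the data have been analysed, so on that footing the change could be made without knowledge of results.

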**Discussion:**

This will be the first randomised controlled trial to combine PRT and a-tDCS targeting balance and gait in people with PD. The study will elucidate the functional, clinical and neurophysiological outcomes of combined PRT and a-tDCS. It is hypothesised that combined PRT and a-tDCS will significantly improve lower limb strength, postural sway, gait speed and stride variability compared with PRT with sham tDCS. Further, we hypothesise that pre-frontal cortex activation during dual-task cognitive and gait/balance activities will be reduced, and that M1 excitability and inhibition will be augmented, following the combined PRT and a-tDCS intervention.

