## Methods/design

### Aims

The primary aim of this pilot study is to determine the effects of a 6-week lower limb balance and PRT intervention with concurrent a-tDCS on gait, balance, strength and UPDRS motor scores in patients with PD. In addition, we will investigate neurophysiological adaptations in M1 excitability and pre-frontal cortex (PFC) activation as potential underlying mechanisms. It is hypothesised that the combination of PRT and a-tDCS will produce favourable functional motor outcomes and neuroplasticity beyond the effects of PRT alone.

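### The named 3-arm by 4-visit ANOVA does not make the hypothesised comparison, a-tDCS against sham at T6, the deciding test, and it omits UPDRS-III

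*Protocol article*

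**What the plan says.** The hypothesis compares two arms that both train. The abstract expects that the combination "will significantly improve lower limb strength, postural sway, gait speed and stride variability compared with PRT with sham tDCS". The Aims section says that it "will produce favourable functional motor outcomes and neuroplasticity beyond the effects of PRT alone", and the main Discussion repeats the comparison with sham.

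The section on sample size and statistical analysis fixes the time point: "Gait speed, static balance and UPDRS-III at T6 will serve as primary outcome measures". It then names one test, a two-way repeated-measures mixed ANOVA "with factors time (T0 vs. T3 vs. T6 vs. T9) and treatment (a-tDCS vs. sham vs. control", which "will be used to determine any effect of the intervention on balance, gait speed and measures of brain physiology". The next sentence adds a follow-up: "False discovery rate analysis will be applied to determine when and where significance is found".

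Under Study overview, the a-tDCS and sham arms both do resistance and balance training, while the control arm has standard care and attends assessments only.

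**The concern.** The omnibus null is that all three arms have the same profile over all four visits. The hypothesis concerns one pair of arms at one visit. Two arms train and one does not, and the Background expects training to work, so the omnibus null may well be false for reasons unrelated to tDCS. A significant interaction would then not answer the trial's question.

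The follow-up sentence may lead to the right comparison, but it names neither a-tDCS against sham nor T6, and it does not define the family of tests. Which result decides the trial is left open. If the hypothesised contrast is reached only after an omnibus test and shares its error rate with other pairs and visits, power is lost in a trial of 14 per arm. In addition, the outcomes listed for the ANOVA are balance, gait speed and brain physiology, so UPDRS-III has no named analysis although it is primary.

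**Working it through.** **The plan's own figure.** The protocol states 14 per arm, at least 80 % power and 5 % significance for a 10–15 % difference in gait speed and static balance. It gives no SD and does not say which arms differ, so the figure cannot be reproduced. Only the implied standardised difference for two arms can be solved (two-sided test assumed):

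d = (1.96 + 0.84) × √(2/14) = 1.06.

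A 10–15 % difference then needs an SD of 10/1.06 to 15/1.06, about 9–14 % of the mean. This neither confirms nor refutes the sample size.

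**Why the omnibus test cannot separate exercise from tDCS.** Write the T6 effects in the order a-tDCS, sham, control.
- Exercise only, (d, d, 0): deviations from the mean are d/3, d/3, −2d/3, with sum of squares d²(1 + 1 + 4)/9 = 2d²/3.
- tDCS only, (d, 0, 0): deviations are 2d/3, −d/3, −d/3, with the same sum of squares, 2d²/3.

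With equal arms and the same time course, the interaction test rejects equally often in both cases.

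**Assumptions not in the document.** 14 per arm with complete data, SD 1, equal correlation rho between visits, effect 0 / 0.5 / 1 / 0.7 of its T6 value at T0 / T3 / T6 / T9, and T6 effect 0.8 SD.

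**Interaction test.** The profile mean is 0.55 and the squared deviations sum to 0.53. The noncentrality is 14 × (2/3 × 0.8²) × 0.53 / (1 − rho), on 6 and 117 df.
- rho 0.6: 7.9, rejection probability about 50 %.
- rho 0.8: 15.8, rejection probability about 84 %.

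Simulation of the exercise-only case gives 48 % and 84 %.

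**Single contrast, a-tDCS against sham at T6, adjusted for T0.** The noncentrality is 0.8 / √[(2/14)(1 − rho²)], on 25 df.
- rho 0.6: 2.65, power about 72 % (70–72 % with simulation).
- rho 0.8: 3.53, power about 92 %.

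The control arm does not enter, so these do not depend on the exercise effect.

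**Follow-up as the plan might be read.** The assumed reading is the interaction test first, then Benjamini-Hochberg over nine change-score comparisons (three pairs at T3, T6 and T9). The table gives the percentage of simulated trials, rho 0.6 / 0.8.

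| True effects at T6 | Interaction significant | a-tDCS v sham at T6 found after follow-up | Single adjusted contrast |
|---|---|---|---|
| Exercise 0.8, tDCS 0 | 48 / 84 | about 2 / 2 | about 5 / 5 |
| Exercise 0, tDCS 0.8 | 50 / 84 | 33 / 72 | 70–72 / 92 |
| Exercise 0.8, tDCS 0.8 | 97 / 100 | 49 / 85 | 70–72 / 92 |

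In the second row the gate alone caps power at 50 % for rho 0.6. In the third row the gate is almost always passed, and most of the loss comes from sharing error over other pairs and visits. Part of the gap in both rows is baseline adjustment: the ratio of adjusted to change-score variance is (1 − rho²) / [2(1 − rho)] = (1 + rho)/2, or 0.8 and 0.9.

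**The case against.** The strongest reply is that the omnibus test is not the last step. When and where most naturally mean visit and pair of arms, so a-tDCS against sham at T6 may well be examined. This stands, and it rules out a stronger reading: a reader might infer that the trial would wrongly credit tDCS in 48–84 % of cases. It would not. That figure is how often the omnibus test correctly detects that exercise works. After the assumed follow-up, a false a-tDCS against sham result at T6 appears in about 2 % of trials, or 3–4 % if the family is only the three pairs at T6.

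The power loss also depends on the family. With three T6 pairs and both effects present, the follow-up finds the tDCS effect in 60 % (rho 0.6) and 90 % (rho 0.8) of trials, against 70 % and 91 % for the adjusted contrast. At high correlation that is a small loss.

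Two further inferences are not supported. Entering T0 as an outcome level dilutes the treatment main effect but does not make it uninterpretable, and the plan does not call it the deciding test. The ANOVA's need for complete rows is not a defect, since multiple imputation and sensitivity analyses for non-random attrition are planned.

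It is also fair that the study is a pilot, that a three-level factor suits the broad aim, and that contrasts and families are often left to an analysis plan. The last point does not dispose of the matter: the protocol itself fixes the omnibus ANOVA as the test of the intervention, which does not match its hypothesis and time point. Its Discussion also claims that any clinically significant benefit of adding a-tDCS will be detected, and that rests on the contrast the named test does not isolate.

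**Conclusion.** The concern holds in a limited form, as a point that should be fixed. The hypothesis is a-tDCS against sham and the primary visit is T6, but the named analysis is a three-arm, four-visit omnibus test that exercise alone can make significant. The follow-up step probably protects against false tDCS claims. It does not settle which comparison decides the trial.

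The cost is mainly power for the hypothesised effect: about 33–49 % against 70–72 % at rho 0.6, and 72–85 % against 92 % at rho 0.8. These figures rest on an assumed correlation, time profile, 0.8 SD effect, omnibus gate and nine-test family, none of which the document gives. The mismatch itself does not depend on them. The omission of UPDRS-III from the ANOVA sentence is plain from the text; it may be loose wording and does not show that UPDRS-III will go unanalysed.

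**What to change.** For each primary outcome (gait speed, static balance and UPDRS-III), state that the primary analysis is the a-tDCS minus sham difference at T6, adjusted for the T0 value, with a 95 % confidence interval. Use ANCOVA at T6, or a mixed model with T3, T6 and T9 as outcomes and baseline as a covariate. Make comparisons with control, the other visits and the global interaction secondary, under the false discovery rate procedure with its family listed. Tie the power statement to the a-tDCS against sham contrast. Keep the planned multiple imputation and sensitivity analyses.

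The cost is analysis wording only: T0 is already collected. Recruitment was still open at publication and allocation is to stay concealed until the data have been analysed, so the change can be recorded before unblinding.
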